# Impact of an Automated Population-Level Cirrhosis Screening Program Using Common Pathology Tests on Rates of Cirrhosis Diagnosis and Linkage to Specialist Care (CAPRISE): Protocol for a Pilot Prospective Single-Arm Intervention Study

**DOI:** 10.2196/56607

**Published:** 2024-05-22

**Keywords:** noninvasive tests, cirrhosis, population health, screening, liver cirrhosis, liver, compensated, risk factor, pathology, population based, liver screening, prevalence, hepatocellular carcinoma, transient elastography, FibroScan

## Abstract

**Background:**

People with compensated cirrhosis receive the greatest benefit from risk factor modification and prevention programs to reduce liver decompensation and improve early liver cancer detection. Blood-based liver fibrosis algorithms such as the Aspartate Transaminase–to-Platelet Ratio Index (APRI) and Fibrosis-4 (FIB-4) index are calculated using routinely ordered blood tests and are effective screening tests to exclude cirrhosis in people with chronic liver disease, triaging the need for further investigations to confirm cirrhosis and linkage to specialist care.

**Objective:**

This pilot study aims to evaluate the impact of a population screening program for liver cirrhosis (CAPRISE [Cirrhosis Automated APRI and FIB-4 Screening Evaluation]), which uses automated APRI and FIB-4 calculation and reporting on routinely ordered blood tests, on monthly rates of referral for transient elastography, cirrhosis diagnosis, and linkage to specialist care.

**Methods:**

We have partnered with a large pathology service in Victoria, Australia, to pilot a population-level liver cirrhosis screening package, which comprises (1) automated calculation and reporting of APRI and FIB-4 on routinely ordered blood tests; (2) provision of brief information about liver cirrhosis; and (3) a web link for transient elastography referral. APRI and FIB-4 will be prospectively calculated on all community-ordered pathology results in adults attending a single pathology service. This single-center, prospective, single-arm, pre-post study will compare the monthly rates of transient elastography (FibroScan) referral, liver cirrhosis diagnosis, and the proportion linked to specialist care in the 6 months after intervention to the 6 months prior to the intervention.

**Results:**

As of January 2024, in the preintervention phase of this study, a total of 120,972 tests were performed by the laboratory. Of these tests, 78,947 (65.3%) tests were excluded, with the remaining 42,025 (34.7%) tests on 37,872 individuals meeting inclusion criteria with APRI and FIB-4 being able to be calculated. Of these 42,025 tests, 1.3% (n=531) had elevated APRI>1 occurring in 446 individuals, and 2.3% (n=985) had elevated FIB-4>2.67 occurring in 816 individuals. Linking these data with FibroScan referral and appointment attendance is ongoing and will continue during the intervention phase, which is expected to commence on February 1, 2024.

**Conclusions:**

We will determine the feasibility and effectiveness of automated APRI and FIB-4 reporting on the monthly rate of transient elastography referrals, liver cirrhosis diagnosis, and linkage to specialist care.

**Trial Registration:**

Australian New Zealand Clinical Trials Registry ACTRN12623000295640; https://tinyurl.com/58dv9ypp

**International Registered Report Identifier (IRRID):**

DERR1-10.2196/56607

## Introduction

### Background

Liver cirrhosis is a major global public health threat; from 1990 to 2017, the global estimate of compensated cirrhosis prevalence increased from 66 million cases to 112 million cases [1], and liver cirrhosis directly causes millions of deaths each year due to liver failure and liver cancer [2,3]. Without timely treatment of chronic liver disease of any cause, individuals are at risk of developing liver cirrhosis [4].

People with compensated cirrhosis receive the greatest benefit from risk factor modification and prevention programs to reduce liver decompensation and improve early liver cancer detection [1]. Curative options are available for early-stage hepatocellular carcinoma; however, most cases are diagnosed at an advanced stage and median survival is only 18% [5], highlighting the importance of early diagnosis [6]. Early-stage liver hepatocellular carcinoma can be identified through surveillance with 6 monthly liver ultrasounds in people with cirrhosis. It is, therefore, imperative that novel population-based screening strategies are explored to identify people with cirrhosis early to facilitate timely linkage to specialist care, including liver cancer surveillance programs.

Transient elastography (FibroScan) has revolutionized the diagnosis of cirrhosis for people with liver disease, providing a noninvasive alternative to liver biopsy [7]. However, at a population level, transient elastography is an unsuitable screening method for cirrhosis due to limited access and cost. Blood-based biomarker algorithms that use readily available blood test parameters, such as the Aspartate Transaminse (AST)–to-Platelet Ratio Index (APRI) [8] and Fibrosis-4 (FIB-4) index [9], have, therefore, been developed as an affordable, accessible screening tool for liver cirrhosis that can triage the need for transient elastography [10].

### Prior Work

Studies in the United Kingdom have used specialized software to automate reflex FIB-4 calculation and reporting on frequently requested blood tests in primary care practice, to increase the diagnosis of people with liver disease and link them to specialist care within public-funded National Health Service networks of the United Kingdom [11,12]. While the iLFT (Intelligent Liver Function Testing) program has proven effective, it requires significant resourcing and may be challenging to translate to privately funded primary care models in countries such as Australia. In contrast, automated reporting of liver fibrosis indices such as APRI and FIB-4 on routinely ordered blood tests by pathology providers does not require specialized software or resourcing and facilitates broad accessibility of results to patients and health workers.

### Study Goal

In this study (CAPRISE [Cirrhosis Automated APRI and FIB-4 Screening Evaluation]), we will determine the feasibility and effectiveness of automated APRI and FIB-4 reporting and provision of brief liver cirrhosis information on the monthly rate and proportion of transient elastography referrals, liver cirrhosis diagnosis, and linkage to specialist hepatology care. We have partnered with a large pathology service in Victoria to pilot a population-level liver cirrhosis screening package, which comprises automated calculation and reporting of APRI and FIB-4 on routinely ordered blood tests and provision of brief information about liver cirrhosis and a web link for transient elastography referral.

### Hypothesis

Automated calculation and reporting of APRI and FIB-4 on routinely ordered blood tests and provision of information about liver cirrhosis, including a link for transient elastography referral, will increase the diagnosis of liver cirrhosis and linkage to specialist care.

### Objectives

The primary objectives of this study are given below.

First, this study aims to measure the monthly rate and the number (proportion) of individuals with APRI greater than 1.0 and FIB-4 greater than 2.67 among people who undergo automated APRI and FIB-4 calculation on blood test events performed through a single Australian pathology service.

Second, this study aims to measure the monthly rate of transient elastography referrals received after the introduction of automated APRI and FIB-4 reporting, compared with the preintervention period.

Third, this study aims to measure the monthly rate and the number (proportion) of transient elastography tests performed in those with an elevated APRI and or FIB-4 score during the intervention period, compared with the preintervention period.

Fourth, this study aims to measure the monthly rate and the number (proportion) of individuals with APRI greater than 1.0 or FIB-4 greater than 2.67 that have cirrhosis range median stiffness (kPa) confirmed on FibroScan.

Finally, this study aims to measure the number (proportion) of individuals with cirrhosis range FibroScan during the intervention period that is linked to specialist care, compared with the preintervention period.

The secondary objective of this study is to describe the sociodemographic factors associated with (1) APRI greater than 1.0 and FIB-4 greater than 2.67, (2) attendance at FibroScan appointment, (3) cirrhosis diagnosed on FibroScan, and (4) linkage to specialist care.

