### Definitions

#### Comparator Group (Standard of Care)

Currently, APRI and FIB-4 scores are not routinely reported anywhere in Australia. Prior to the intervention, blood tests will be reported per standard of care. APRI and FIB-4 scores will be calculated automatically by the pathology service from the start of the study but will not be reported to ordering clinicians until the intervention period. FibroScans are requested through a paper-based referral form by general practitioners or specialists, which is then faxed to the hospital for triage and booking.

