### Statistical Analysis Plan

#### Outcome Measures

Data will be analyzed per test event and per individual tested.

Primary outcomes of this study include the number of APRI and FIB-4 scores calculated on blood test events conducted during the study period, overall and per month; the number (proportion) of APRI scores that are greater than 1.0 and FIB-4 scores that are greater than 2.67; number of FibroScan referrals overall and per month, operationalized as number of completed FibroScan referrals generated online using the recommended St Vincent’s Pathology FibroScan referral link on the request slip, or St Vincent’s Pathology APRI or FIB-4 calculation web page referral form link; number of individuals with an APRI greater than 1.0 or FIB-4 score greater than 2.67 who undergo a FibroScan test at St Vincent’s Hospital Melbourne overall and per month; proportion of individuals with an APRI greater than 1.0 or FIB-4 score greater than 2.67 who undergo a FibroScan test at St Vincent’s Hospital Melbourne; the number of individuals per month who undergo FibroScan at St Vincent’s Hospital Melbourne who have cirrhosis diagnosed (liver stiffness measurement >12.5kPa); the number (proportion) of individuals with an APRI greater than 1.0 or FIB-4 score greater than 2.67 who have cirrhosis confirmed by FibroScan; the number (proportion) of individuals with etiology-specific cirrhosis range FibroScan results that are referred to the specialist liver clinic; and the number (proportion) of individuals with etiology-specific cirrhosis range FibroScan results that attend to the specialist liver clinic appointment.

The secondary outcomes of this study include the number (proportion) of individuals, stratified by age category, sex, and postcode who have elevated APRI greater than 1.0 and FIB-4 score greater than 2.67, attend the FibroScan clinic for further testing, have etiology-specific cirrhosis range FibroScan scores (kPa), and attend a liver specialist clinic appointment.

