### Analysis Methods

The number of APRI and FIB-4 scores generated and the proportion of APRI and FIB-4 scores in the cirrhosis range will be described overall and rates per month will be calculated.

The number (proportion) of individuals with an elevated APRI or FIB-4 who are referred for a FibroScan will be described overall and per month; and the number of FibroScan referrals after the intervention will be compared with the number of FibroScan referrals prior to the intervention by logistic regression modeling (time series analysis with the timepoint of interruption defined as February 1, 2024, when the reported APRI score intervention was introduced).

Similarly, the number (proportion) of individuals with an elevated APRI or FIB-4 who are referred for a FibroScan and who attend their FibroScan appointment, overall and per month, will be described and compared with the number (proportion) of FibroScan appointments attended prior to intervention using linear regression modeling, as well as the number (proportion) of individuals with FibroScan results in cirrhosis range that are referred and attend specialist liver clinic appointments.

The number and proportion of individuals with an elevated APRI or FIB-4 who had cirrhosis confirmed by FibroScan will be described, and sensitivity, specificity, and positive and negative predictive values of APRI for cirrhosis determined by confusion matrix. The area under the receiver operating characteristic curve of APRI and FIB-4 for cirrhosis diagnosis will also be calculated by receiver operating characteristic analysis.

The bivariate distribution of sociodemographic (sex, age category, and urban or regional place of residence [defined by postcode using SEIS data]) and clinical variables (liver disease indication) within the proportion of people with elevated APRI and FIB-4 score, who attend FibroScan testing, have elevated FibroScan results, and attend the liver specialist clinic will be determined and compared with their counterparts using chi-square test for categorical data, 2-tailed Student *t* test for parametric continuous data, and Wilcoxon rank-sum test for nonparametric continuous data as appropriate.

A 2-tailed *P* value of .05 will be used as the significance threshold for all analyses. All analyses will be performed using STATA (version 17; Stata Corporation).

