### Sample Size Justification

We have conducted a preliminary analysis of the number of AST and platelet count testing events that were performed at St Vincent’s Pathology over a 12-month period (2019). These data showed approximately 11,000 people known to St Vincent’s hospital clinics, and a further 4400 people in the community that had AST and platelet count testing events, that would have allowed APRI calculation to be performed, proving the feasibility of reaching large numbers within the community for cirrhosis screening.

For the comparison of rate of referral for FibroScan before and after the intervention, we estimate that we will be powered to detect a 10% difference in rates of FibroScan referral before and after the intervention. For the logistic regression analyses to determine the difference in proportion of APRI scores leading to referral before and after providing cirrhosis information and FibroScan referral link information (overall and by subgroup), and for determining the proportion of FibroScan referrals that are attended (overall and by subgroup), we are powered to detect a 5% or greater difference between the intervention and historical control groups with power 90% and a sample size of 1100 per subgroup. The above numbers of more than 15,400 individuals having APRI calculations within 12 months suggest that we will be adequately powered to explore our end points including stratified by sex, urban versus rural place of residence, age category, socioeconomic quartile of place of residence, and indication for FibroScan (all of which are expected to have >1000 individuals in each subgroup).

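### The before/after referral comparison counts referrals rather than people, while the intervention adds a second referral form and a repeated prompt; duplicates would bias it toward the intervention, by an amount the protocol does not let one establish

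*Protocol article*

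**What the plan says.** All references are to the protocol article.

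- **Objectives.** The second primary objective is to "measure the monthly rate of transient elastography referrals received after the introduction of automated APRI and FIB-4 reporting", compared with the preintervention period. The unit is the referral.
- **Outcome Measures.** The number of referrals is "operationalized as number of completed FibroScan referrals generated online using the recommended St Vincent’s Pathology FibroScan referral link", or the equivalent link on the pathology web page. The same section states that "Data will be analyzed per test event and per individual tested", and its scan, cirrhosis and specialist-clinic outcomes count individuals.
- **Analysis Methods.** For people, "The number (proportion) of individuals with an elevated APRI or FIB-4 who are referred for a FibroScan will be described overall and per month". The before/after test that follows is on referrals: "the number of FibroScan referrals after the intervention will be compared with the number of FibroScan referrals prior to the intervention".
- **Comparator Group (Standard of Care).** Before the intervention, "FibroScans are requested through a paper-based referral form by general practitioners or specialists, which is then faxed to the hospital".
- **Intervention Period.** A web form separate from the fax form is added, and the link to it goes on every report for which the scores are calculated.
- **Sample Size Justification.** The authors estimate that "we will be powered to detect a 10% difference in rates of FibroScan referral before and after the intervention". A later sentence there refers to the proportion of referrals that are attended.

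**The concern.** A count of forms equals a count of people only if each person generates one form, or if forms per person are the same in both phases. The design gives reason to doubt the second condition. In the first six months the only route described is the fax. In the next six there are two routes, and the prompt recurs each time a patient has another qualifying blood test. A patient already referred by fax can also be sent through the web form, and a patient retested can be sent again. Both sources of extra forms arise in the intervention phase only, so any bias on an all-route count runs in favour of the intervention.

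At stake is the reading of the result. More forms per patient would look like more people being sent for cirrhosis assessment. Where attendance is expressed per referral, duplicates also enlarge the denominator without adding an attended scan.

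**Working it through.** **1. The plan's own figure.** The 10% detectable difference comes with no baseline count, power or statement of scale, so it cannot be reproduced. As an indication, treat the two phases as Poisson counts with a rate ratio of 1.1, two-sided 0.05. The preintervention count needed is (z_α/2 + z_β)² × (1 + 1/1.1) / (ln 1.1)². This gives about 1,650 referrals for 80% power and 2,208 for 90%. The article gives no referral count to set against these.

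**2. Which referrals are counted.** Two readings are possible.
- *Web forms only (Outcome Measures).* A fax-plus-web pair counts once. The preintervention count is zero, or close to it if the web page announced about a month ahead already carried the form link. A 10% relative change then has no usable base.
- *All routes (what the comparison in Objectives and Analysis Methods needs).* The comparison can be made, but a fax-plus-web pair counts twice.

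Repeat web forms for one person count more than once under either reading.

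**3. Repeat testing, from Results and Table 1 (preintervention).**
- All tests: 42,025 / 37,872 = 1.110 per person.
- APRI above 1: 531 / 446 = 1.191 per person, or 85 repeat elevated tests.
- FIB-4 above 2.67: 985 / 816 = 1.207 per person, or 169 repeat elevated tests.

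These are blood tests per person, not referrals. They serve below only as assumed values for web forms per person.

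**4. Repeat prompts to newly referred people.** Let B people be referred by fax in each phase and N new people by web in the second, with w forms each. Forms rise by wN/B. If that rise is 10%, people rise by N/B = 0.10/w.

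| w (assumed) | Rise in people | Due to duplicates |
|---|---|---|
| 1.110 | 9.0% | 1.0 point |
| 1.191 | 8.4% | 1.6 points |
| 1.207 | 8.3% | 1.7 points |

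Most of such a rise is real.

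**5. Second forms for people already referred by fax.** If a share d of the B fax-referred people also receive a web form and nobody new is referred, forms rise by d and people by 0. With d = 0.10 (assumed), forms rise 10.0% and people 0.0%. The chance of a significant rise in forms is approximately 1 − Φ[(1.96√(2.1B) − 0.1B) / √(2.3B)]. The term 2.3B is the variance of the difference, B + 1.3B, since a person contributes one form with probability 0.9 and two with probability 0.1.

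| B per 6 months (assumed) | Chance of a significant rise |
|---|---|
| 100 | 0.11 |
| 300 | 0.23 |
| 600 | 0.40 |
| 1,000 | 0.58 |
| 1,650 | 0.79 |

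On a count of people, the upper-tail rate in the same scenario is 0.025.

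**6. Could repeat elevated tests alone supply 10% of baseline?** The share of the 169 repeat FIB-4 tests that would have to yield a duplicate form is 0.1B/169: 18% at B = 300, 59% at B = 1,000 and 98% at B = 1,650.

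**The case against.** The strongest reply is that a de-duplication rule is ordinary content of an analysis plan or data dictionary, and only a condensed article is at hand. That stands: the absence of such a rule is not the finding. The finding is that the article fixes the compared unit as referrals and leaves people to description, and that its operational definition does not fit the comparison.

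Second, under the web-only definition a fax-plus-web pair counts once, so cross-route duplication disappears. That is correct, but the same definition removes the preintervention count.

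Third, person-level outcomes are already planned for scans, cirrhosis and linkage, and a duplicate form cannot inflate diagnosis or linkage, which are what the hypothesis concerns. This stands and limits the damage to the referral comparison. Referral volume is also a legitimate service measure in a pilot.

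A reader might infer from the 1.19 and 1.21 elevated tests per person that forms would exceed people by 19 to 21%, about twice the 10% target. The documents do not support that. The ratios are preintervention blood tests, no referral rate per report is given, and step 4 shows that repeat prompts to new referrals leave most of a 10% rise genuine. Nor is the study shown to be sized on the 10%: it runs for fixed calendar periods, and no calculation is given.

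Finally, the attendance effect is limited. The Preintervention Period section uses scheduled appointments, which a duplicate form affects only if it is booked separately. The effect follows directly only from the per-referral wording in Sample Size Justification.

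**Conclusion.** The point holds as a defect in the stated unit and definition of the referral outcome. The tested quantity is a count of referrals, its operational definition leaves no usable preintervention count, and on the all-route count that the comparison needs, duplicates can arise in the intervention phase only and favour the intervention.

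The size is not established. If web forms per new person match observed tests per person, duplicates make up about 1.0 to 1.7 points of a 10% rise. A 10% rise made wholly of duplicates requires, under all-route counting, second forms for about 10% of fax-referred people with no new person referred. Nothing in the article shows that this rate will occur. The baseline counts, duplication rates and Poisson variation used above are all assumptions. The conclusion that duplicates will produce the detectable difference goes further than the documents allow; they can contribute to it and, with enough cross-route duplication, could produce it. The change is worth making because it is cheap and also resolves the conflict over which referrals count.

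**What to change.** In Objectives, Outcome Measures and Analysis Methods, define the compared referral outcome identically in both phases: the number of distinct individuals with at least one FibroScan referral by any route (fax or web) per month, counting the first referral per person per phase. Have the booking team remove duplicates by patient record before the deidentified data are released, since they may not be separable afterwards. Keep raw forms by route as a descriptive measure of workload and of use of the web link. Use distinct individuals referred as the denominator wherever attendance is expressed per referral, as in Sample Size Justification.

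The cost is rewording and one step in the booking extract. The downside is that genuine re-referrals within a phase no longer count in the comparison, although they remain visible in the raw form counts.
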